#### Resource use

Resource use related to BC diagnosis and treatment will be collected via an adapted version of the UK Cancer Costs Questionnaire (UKCC) Version 2.0 [51]. The UKCC collects data on the number of contacts with health professionals outside the hospital setting (general practitioner, nurse, as well as other medical and non-medical specialities), the number of emergency room visits and the medication taken. Other non-medical resources incurred by the family, such as the use of personal social services to help in daily activities, travel and transportation costs, as well as other costs related to a diverse array of goods and services the patient has used to deal with BC, are also collected by the questionnaire. In addition, the questionnaire has a section devoted to collecting data about the time taken off work due to BC, which will be used to estimate productivity losses.

*Immunology and epigenetics markers* (study 1 only). Blood samples will be collected, stored and analysed as stated in Sect. 33.

*ACT processes* (subsample of study 1 only). Hexa(in)Flex Interview is a semi-structured interview that aims to assess qualitatively the subjective experience of the six core processes of the Psychological (In)Flexibility Model underlying ACT, in women with BC. This interview was developed within the context of this project. It comprises two parts: (a) an introduction to the aims of the interview, as well as introductory questions regarding diagnostic information (e.g. duration of diagnosis, treatment phase, support network) and general coping and adaptation to the cancer diagnosis; (b) five sections of open questions aiming to assess experiential avoidance versus acceptance, cognitive fusion versus defusion, conceptual versus contextual self, past and future conceptualised (auto-pilot) versus contact with present moment, and lack of values clarity and action versus commitment to valued action. Each section has instructions on how the interviewer should conduct the questioning, as well as additional tips and caveats that should be considered.

#### Acceptability of the intervention

At the end of the intervention, participants will complete a final evaluation form of the programme assessing several aspects, including the match between their expectations and the actual intervention, their overall level of satisfaction with the programme, the perceived usefulness of the intervention to help them cope with their problems and solve their difficulties, and their intention to recommend or use the programme in the future if necessary, among other aspects.

#### Feasibility of the intervention

It will be measured through participants’ adherence, including the number of sessions attended, the proportion of treatment completers (defined as those who participated in at least 75% of the sessions) and the number of homework practices completed between each session. Dropout rates (i.e. the proportion of participants that dropped out from the intervention before completing it) will also be considered as an indicator of feasibility.

### Additional variables

#### Sociodemographic and clinical variables

Variables such as age, education level, marital status, residency area, household composition and income, BC diagnosis, BC stage, TNM classification, time since BC diagnosis, immunohistochemical data, values of CA15.3, haemoglobin, leukocytes, and platelets, fertility preservation, previous chemotherapy treatment (and number of cycles), use of psychopharmacological medication, and relevant clinical history will be collected.

#### Major life events

The Major Life Events Questionnaire (MLEQ; [52]) assesses the occurrence of major life events in the previous 12 months. The MLEQ was based on the Psychological Stress Index [53] and comprises 22 items that represent possible major life events (e.g. marriage, divorce, pregnancy, interpersonal conflict, death of a significant other). For each item, participants report the occurrence or non-occurrence of a specific event during the previous 12 months.

#### Psychological processes awareness

The Awareness of Contextual Therapies Processes Scale was developed by the authors of these studies to assess the extent to which participants increase their awareness of the psychological processes and mechanisms involved in the intervention.

#### Home practice frequency

At each session of the Mind programme intervention, participants will be asked about whether they had completed the at-home practice that was assigned in the previous session.

#### Efficacy expectancy

Participants will answer the following yes–no single question about the efficacy expectancy at baseline: “Do you believe that the intervention will bring benefits to your quality of life and mental health?”.

## Plans to promote participant retention and complete follow-up {18b}

Outcome self-report measures will be completed online so that participants may access them at convenient times and places. Participants will receive automated assessment survey invitations and reminders. Dedicated staff members (see Sect. 19) will review participants’ responses and send reminders by email or text if assessment surveys are not complete, until the completion of the assessment period. A database checklist will be available to ensure that all measures are being collected according to the schedule. Participants will also receive a 25€-worth gift voucher for their full participation, at the 6-month follow-up.

Irrespective of intervention discontinuation or deviation from protocol, outcomes data collection will continue for all participants. A variable representing the extent of treatment completion (number of sessions attended) will be added, and sensitivity analyses to evaluate its impact on intervention outcomes will be performed.

### Data management {19}

Data management will be performed in accordance with the European regulations for data processing [54] and the University of Coimbra’s guidelines [55]. There are designated team members to enter, code, protect and store data. During the course of the project, these researchers will enter and code information, collected throughout recruitment, intervention and assessment phases, in a statistical analysis software file using unique participant IDs to identify participants. These researchers will have access to participants’ identifiable data and safeguard it in a secure password-protected local drive. They will also be responsible for preparing database checklists and alerts, sending reminders, monitoring data irregularities (e.g. skip patterns, out of range data, completion times), sharing de-identified data with lead statisticians and granting access to authorised entities conducting trial-related monitoring, audits and inspections. Measures scoring will be done via syntax to minimise errors. After project termination, data, stored in a secure password-protected local drive, will be kept for 5 years, before disposal.

### Confidentiality {27}

Personal information about potential and enrolled participants will be collected during the screening interview (face to face or via phone call) and stored in a secure password-protected local drive (see Sect. 19). The database containing research records will use unique participant ID to promote data sharing. The primary source of data will come from self-reported measures hosted on LimeSurvey, a secure web-based data collection platform. Only designated team members will have access to participants’ identifiable data. De-identified data will be shared on need and solely among the research team.

### Plans for collection, laboratory evaluation and storage of biological specimens for genetic or molecular analysis in this trial/future use {33}

Blood samples will be collected in vials with no anti-coagulation factors, at the Radiotherapy Service of CHUC, with the collaboration of the Service. All patients will be asked for the presence of infection symptomatology (e.g. flu, cold) at the blood collection time and on the previous 15 days. Samples will be maintained at 4 °C until and during transport to the Laboratory of Molecular Pathology (at Portuguese Institute for Oncology at Coimbra Francisco Gentil) where they will be processed. Sample processing involves serum collection through centrifugation, which is performed within 1 h (maximum 2 h, but these situations are documented) after blood collection. Serum samples will be stored at − 80 °C until analysis. Cytokines will be quantified by flow cytometry at the Molecular Pathology Laboratory and epigenetic studies will be performed at Institute of Molecular Pathology and Immunology of the University of Porto, through quantification of microRNAs. After project termination, samples and data will be safely stored for 5 years and then disposed of. Their future use in ancillary studies is not yet planned.

## Statistical methods

### Statistical methods for primary and secondary outcomes {20a}

#### General analytic procedures

The superiority of the Mind programme over the control group(s) will be tested through the analysis of changes in the primary (cancer-specific QoL) and secondary outcomes (anxiety and depressive symptoms, psychological flexibility, self-compassion, health-related QoL, resources consumption), controlling for sociodemographic and clinical variables and potential moderation effects of variables such as the awareness of psychological processes, the frequency of at-home practice, the number of major life events occurring during the previous year and efficacy expectancy. The Mind programme will be compared against the support group in study 1 and against both the support and treatment as usual (waiting list) groups in study 2. Study 1 also includes immunological and epigenetic markers as secondary outcomes. The analytical approaches for both studies are otherwise comparable.

#### Analyses by aims

Aim 1: Determine the efficacy of the Mind programme compared to an active (i.e. support group) and/or inactive (i.e. treatment as usual group) control condition at post-intervention and at 6-month follow-up period.

The planned analysis for each outcome is a repeated-measures linear mixed model, including polynomial simple slopes to identify non-linear change over time. Within-group and contemporaneous between-group post hoc comparisons, using independent- or paired-samples *t*-tests (as appropriate), adjusted for multiple comparisons using the modified Bonferroni adjustment, will be performed. The efficacy of the intervention can be inferred through the evaluation of the simple slopes for each treatment condition, whereby the experimental condition demonstrates a significant improvement in QoL scores over time, and this improvement exceeds that of the control condition. The clinical significance of changes presented by each participant will be determined by computing the reliable change index (RCI) and considering mixed models of repeated measures (i.e. growth modelling analysis). In the former, we will calculate primary or secondary outcome RCI for each participant between pre- and post-intervention, as well as pre-intervention and 6 months. An RCI of ± 1.96 is considered statistically significant at *p* = 0.05, and the proportions of participants within each treatment condition who demonstrate significant improvement, decline and no change will be recorded. Fisher’s exact test will be used to examine for significant differences in the proportion of change between treatment allocations. Finally, we will perform correlation analysis between the raw RCI values and demographic variables separately for each treatment condition. This final analysis is used to examine potential predictors of individual change and the nature of that change.

Aim 2: Determine the cost-effectiveness of the Mind programme compared to an active (i.e. support group) and/or inactive (i.e. treatment as usual group) control condition at post-intervention and at 6-month follow-up period.

The within-trial economic analyses will be carried out in line with standard health economic methods, following the Consolidated Health Economic Evaluation Reporting Standards (CHEERS) checklist [56]. An economic evaluation of each trial will be conducted. Each economic evaluation will include a cost-utility analysis using the outcome quality adjusted life years (QALYs). EQ5D-5L utility scores will be used to estimate QALYs over each trial period using the area under the curve method [57]. Costs will be estimated from two different perspectives, a Portuguese public health care system perspective and a societal perspective. Costs within the public health care system perspective include the cost to run the interventions, including, for instance, therapist costs, as well as other health care costs (other health care utilisation and medication use). In the analysis from a societal perspective, costs beyond the healthcare sector will additionally be included, for instance, social support, and indirect costs (e.g. productivity loss associated with work absenteeism) captured by the UKCC. Costs will be estimated using publicly available unit costs for healthcare services, market process for medications and lost wages for absence from work. Costs per participant will be calculated by multiplying the frequency of each resource by its unit cost. Unit costs will be sourced from publicly available sources.

Costs and QALYs between the Mind programme and the control groups will be compared. Differences in QALYs and costs between the groups will be analysed using generalised linear models to allow for other distributions and functional forms to fit the cost and QALY data [58]. Incremental cost-effectiveness ratios (ICERs) will be estimated, as the ratio between the difference in costs and the difference in QALYs between the Mind programme and the control groups, for each costing perspective. The ICERs will be expressed as additional costs per additional QALY gained. Non-parametric bootstrapping will be carried out to deal with uncertainty around the incremental cost and QALY estimates, which will be represented on cost-effectiveness planes. A cost-effectiveness plane is a scatterplot of the bootstrapped estimates across four quadrants, where each quadrant has a decision implication. Net monetary benefits at different thresholds of willingness to pay will be calculated to determine the proportion of times the Mind programme yields more net benefit than the controls. These proportions will be plotted to generate cost-effectiveness acceptability curves (CEAC), which show the probability of the intervention being cost-effective at different values a decision-maker is willing to pay for a unit of improvement, in this case, a QALY gained [59, 60]. One-way sensitivity analyses will be carried out to test for the impact of changes in assumptions on the robustness of the results.

Aim 3: Determine the contribution of mediators and moderators in treatment effect.

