## Interventions

### Explanation for the choice of comparators {6b}

Both studies include two intervention groups (see Sect. 11a, below): the Mind programme group and the support group. The Mind programme was previously developed and tested and presented good preliminary findings [29]; the comparator is a support group intervention similar to those implemented in prior RCTs conducted in BC patients [30]. The purpose of this comparator group is to control for effects related to group belonging, personal sharing of experiences, and contact with therapists and fellow participants.

A second comparator (inactive control group) is also included in study 2. Both comparators in this study allow time effect control and treatment allocation blindness.

Regardless of the intervention assigned to each participant, all patients will continue receiving the recommended medical treatment for their clinical diagnosis.

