### Intervention description {11a}

#### Mind programme for women with BC (optimised version)

The Mind programme is a manualised psychological intervention tailored to women with BC and intended to be delivered by two licenced psychologists, in a face-to-face or online group format. This intervention comprises 8 weekly group sessions, lasting 90–120 min each. Its content was optimised by the research team based on (a) the intervention’s pilot study results [30]; (b) the research team’s experience in psycho-oncology and/or in delivering similar interventions to patients with chronic medical conditions; (c) previous clinical experience in delivering the Mind programme in its pilot study; and (d) previous clinical experience in delivering the LIFEwithIBD programme, an adaptation of the Mind programme for people with inflammatory bowel disease [31, 32] As part of optimising the intervention (Table 1), modules on shame and self-criticism were improved, and the forgiveness module of the original Mind programme was replaced with a module on gratitude. Some compassion strategies (e.g. Compassionate Image exercise) were replaced by Mindful Self-Compassion practices, and the module on the observing self, as conceptualised by ACT, was removed [33]. Therefore, the optimised Mind programme (Table 1) comprises the following core themes: (a) acceptance of internal experiences, willingness, values and committed action [34]; (b) mindfulness practice [35]; (c) compassion-based practices [e.g. Mindful Self-Compassion [33], Compassion-Focused Therapy [23] and Loving Kindness meditation [36]; and (d) gratitude (towards one’s body) [36]. Educational aspects of physical and mental fatigue were also included. Each session will follow a similar format: (1) meditation practice; (2) discussion about between-session assignments (homework); (3) presentation of the session’s topics and in-session experiential exercises and practices; and (4) mindfulness or compassion meditation practices. Participants will have access to a participants’ manual (including handouts and audio files), which will guide them over the sessions and exercises. The between-session activities (e.g. mindfulness exercises and compassion practices, available through audio files made available through the sessions) are in line with the topics covered in each session and are prescribed to participants for daily practice until the next session. Participants with two missed sessions will be considered intervention non-completers, but they will be allowed to maintain their participation (and included in intention-to-treat analyses). To ensure treatment integrity, the following will be assured: (a) the Mind programme will be delivered in a co-therapy system, by two therapists with (at least) a Portuguese psychologist licence, a MSc degree in Clinical Psychology, and experience and training in ACT, mindfulness and compassion-based interventions; (b) all therapists will follow the intervention manual; (c) by the end of each session, the co-therapist will complete a checklist of the contents discussed in each session to safeguard treatment fidelity.

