#### Support group intervention

This intervention (comparator) comprises 8 weekly 90 to 120-min sessions intended to be delivered by two licenced psychologists, in a face-to-face or online group format. Table 2 presents the BC-related content of the intervention, which will be discussed among participants in each session. The facilitators of this intervention will engage in a purely moderating role (e.g. facilitators should guarantee that all the participants have the chance to participate, and no one will use that time extensively; facilitators should also intervene if a participant states inaccurate information). As it is the case with the Mind programme group, participants with two missed sessions will be considered intervention non-completers, but they will be allowed to maintain their participation (and included in intention-to-treat analyses).

**Table 2 Tab2:** Session content for the support group intervention

Session 1	Participant self-introduction, group rules and discussion of expectations related to the intervention
Session 2	Emotional impact of BC diagnosis
Session 3	BC treatment side effects
Session 4	BC impact on family and caregivers
Session 5	Work-related and physical impact of BC (e.g. fatigue)
Session 6	Body image and sexuality after BC
Session 7	Self-care strategies
Session 8	Conclusion and final remarks

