#### Treatment as usual (waiting list)

The inactive control group (study 2) will receive the usual treatment for cancer patients in Portugal. In this country, the public healthcare system does not offer psychological counselling or psychotherapy as part of the regular care of women with BC. To gain access to this service, a referral from a physician is needed and not always granted due to lack of resources. At the end of this project, the intervention that proves to be most efficacious will be offered to the participants allocated to this condition.

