### Sample size {14}

Regarding study 1, power was considered according to a sensitivity analysis of the likely attainable sample size and compare with the effect sizes estimated by previous meta-analyses and studies suggesting improvements in mood and QoL between SMD = 0.2 to 0.6, favouring psychotherapies over controls [15, 16]. It is anticipated that up to *N* = 150 (*n* = 75 per group) participants will be recruited, and attrition rates of between 10 and 30% can be expected. The planned analysis specifies a repeated-measures linear mixed models analysis, a group allocation of 1:1, alpha of 0.05, a minimum of 80% power, three assessment points and a compound symmetry correlation matrix (rho = 0.5; Lu et al., 2008). Under these parameters, the study is powered to reliably detect a between-group difference on cancer-specific QoL at follow-up of SMD = 0.51 (WebPower; [37]).

For study 2, the GLIMMPSE software was used to calculate the minimum sample size required for a three-armed linear mixed model with three measurements. Assuming a comparable effect size to that estimated in study 1 (SMD = 0.5) favouring the Mind intervention group over waiting list at 6 months for QoL, an unstructured correlation matrix, a group allocation of 2:2:1, alpha of 0.05 and a minimum of 80% power, the minimum sample size required is *N* = 117. To account for up to 30% attrition, this sets the minimum total sample size at *N* = 153 [38].

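### Mind and support are delivered in therapy groups, but the power statements and the named between-arm tests make no allowance for correlation within a group

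*Protocol article*

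**What the plan says.** Below, "arm" means treatment arm and "therapy group" means the women who attend sessions together.

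- **Delivery (Intervention description {11a}).** Of Mind: "This intervention comprises 8 weekly group sessions, lasting 90–120 min each". Of support: "This intervention (comparator) comprises 8 weekly 90 to 120-min sessions intended to be delivered by two licenced psychologists, in a face-to-face or online group format".
- **Role of the group (Explanation for the choice of comparators {6b}).** The support arm is there to "control for effects related to group belonging, personal sharing of experiences, and contact with therapists and fellow participants".
- **Third arm, Study 2.** "The inactive control group (study 2) will receive the usual treatment for cancer patients in Portugal". These women meet in no study group.
- **Sample size {14}, Study 1.** "The planned analysis specifies a repeated-measures linear mixed models analysis, a group allocation of 1:1, alpha of 0.05", with at least 80% power, three assessments and compound symmetry with rho 0.5. With up to 150 women (75 per arm), the detectable SMD is given as 0.51.
- **Sample size {14}, Study 2.** SMD 0.5 for Mind over waiting list at 6 months, an unstructured correlation matrix, 2:2:1 allocation, alpha 0.05 and 80% power. This gives N = 117, raised to 153 for attrition.
- **Analysis {20a}, Aim 1.** "The planned analysis for each outcome is a repeated-measures linear mixed model, including polynomial simple slopes to identify non-linear change over time". Arms are then compared with t-tests, and proportions with reliable change are compared with Fisher's exact test.

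No group size, ICC or design effect appears among the sample-size inputs. Neither therapy group nor therapist is among the examples named as covariates or moderators.

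**The concern.** Women in one therapy group share two psychologists, the same discussions and each other. Whatever makes one group go well or badly affects all its members. The protocol itself lists disruptive conflict within a group as a possible adverse event. A group-based comparator balances the average effect of being in a group across arms. It does not remove the correlation among women who sat in the same group.

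If that correlation is positive, each arm carries less information than its head count suggests. Tests that ignore it give intervals that are too narrow and reject too often, and a power statement that ignores it promises too much. This bears on cancer-specific quality of life, the primary outcome of both trials.

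**Working it through.** **1. Does the stated figure already contain an allowance?** Study 1 was reproduced in two ways, both with women as independent units.
- Repeated-measures F test, N = 150, 2 arms, 3 times: df = 2 and 148 × 2 = 296. With f = 0.51/2 = 0.255, lambda = 0.255² × 150 = 9.75 and power is 80.1%. Solving for 80% gives SMD 0.5095.
- Simple two-sample comparison with 60 per arm (20% attrition): SMD 0.5115.

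Either route gives 0.51 with no clustering, so no allowance is hidden in the figure. Study 2's N = 117 cannot be reproduced, because its correlations and the assumed effect in the support arm are not given.

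**2. Assumptions.** Group size and ICC are not stated. The range used is m = 6 to 12 analysed women per group and ICC 0.01 to 0.10, with m = 8 and ICC 0.05 as a middle case. Tests are taken as two-sided at 5%, and the ICC is that of the contrast tested.

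**3. Formulas.**
- Mind against support, both arms clustered: DE = 1 + (m − 1) × ICC.
- Mind against waiting list at 2:1, only Mind clustered: the variance is proportional to DE/2 + 1 instead of 1/2 + 1, so DE₂ = (DE/2 + 1)/1.5.
- True type I error of the unadjusted test: 2 × [1 − Φ(1.96/√DE)].
- Power where 80% was intended: Φ(2.802/√DE − 1.96).
- Study 1 detectable SMD: 0.51 × √DE.

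**4. Middle case.**
- Mind against support: DE = 1 + 7 × 0.05 = 1.35 and √1.35 = 1.162. Type I error is 2 × [1 − Φ(1.687)] = 9.2%. Power is Φ(0.452) = 67% (66.5% with the F test of step 1). Detectable SMD is 0.51 × 1.162 = 0.59.
- Mind against waiting list: DE₂ = (0.675 + 1)/1.5 = 1.12. Type I error is about 6.4% and power about 76%.

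**5. Range.**

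| m, ICC | DE, Mind v support | Type I error | Power | Study 1 SMD | DE₂, Mind v waiting list | Type I error | Power |
|---|---|---|---|---|---|---|---|
| 6, 0.01 | 1.05 | 5.6% | 78% | 0.52 | 1.02 | 5.2% | 79% |
| 8, 0.05 | 1.35 | 9.2% | 67% | 0.59 | 1.12 | 6.4% | 76% |
| 12, 0.10 | 2.10 | 17.6% | 49% | 0.74 | 1.37 | 9.4% | 67% |

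The design effects and type I errors for Mind against support apply to that comparison in either trial. The SMD column is for Study 1 only. The Study 2 power column starts from a true 80%, which could not be confirmed.

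**6. Number of groups at 8 women each.** Study 1: 75/8, about 9 per arm. Study 2: 153 × 2/5 = 61 women per grouped arm, and 61/8 is about 8.

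**The case against.** The strongest reply is that a condensed article need not spell out random effects. A linear mixed model can hold a therapy-group term, and an unseen analysis plan may add one. That stands for the model. A reader might infer that the woman is the model's only level, or that one error variance is imposed on all arms. The article says neither: it gives no random-effects structure and no residual structure. The reply does not reach two things that the article does fix. The power inputs are listed without clustering, and the ordinary t-tests and Fisher's exact test cannot carry a therapy-group effect.

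A second reply is that the upper figures are built on assumptions. That also stands. The 17.6% needs 12 analysed women per group and ICC 0.10. Twelve enrolled with 30% lost leaves 8.4, hence DE = 1 + 7.4 × 0.10 = 1.74 and a type I error of about 13.7%. The Trial design section reports recruitment too slow to run groups regularly, which gives no support for assuming large groups. At the low end the loss is about 2 points of power.

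Third, the larger figures might be read as applying to every comparison in both trials. They do not. The comparison that sizes Study 2 has one ungrouped arm and is affected less.

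**Conclusion.** The point holds, conditionally. With any positive ICC, the between-arm t-tests and Fisher's test as written understate uncertainty, and the stated power is optimistic. The mixed model will do the same unless a therapy-group term is added.

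The size depends on the assumed group size and ICC. In the middle case, Study 1's detectable SMD of 0.59 lies almost at the top of the 0.2 to 0.6 that the protocol cites as plausible. The effect on Mind against waiting list is in the same direction but milder.

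Two stronger conclusions are not supported. The documents do not show that standard errors are in fact too small, since that needs a positive ICC. They also do not show N = 117 to be wrong by any given amount: it cannot be reproduced, so only the direction can be stated.

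**What to change.** 1. Record a therapy-group identifier for every woman in Mind and support. The article does not list one among its variables.
2. Add a therapy-group random effect to the between-arm mixed models, with Kenward-Roger or Satterthwaite degrees of freedom. In Study 2 use a partially nested form: the random effect in Mind and support only, waiting-list women as singletons, and residual variance allowed to differ by arm.
3. Replace the between-arm t-tests and Fisher's exact test with contrasts from that model, or with tests that respect therapy groups.
4. Restate the detectable SMD or power for each trial over a stated group size and ICC range, separately for Mind against support and Mind against waiting list. No more women need be enrolled.
5. Resampling whole therapy groups in the economic bootstrap is reasonable, but with about 8 or 9 groups per arm it should carry a caveat.

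Cost: one more recorded variable and one more model term, both possible before analysis. Intervals will be wider and the stated detectable effect less favourable. With so few groups the group variance will be imprecise and may be estimated at zero.
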